## Abstract

**Background:**

Acceptance and Commitment Therapy (ACT) has been successfully established in hundreds of efficacy trials. It is less understood, however, how ACT works in real-world settings. Furthermore, little is known about how contextual variables such as treatment setting (inpatient vs. outpatient), social network and environment of the patient impact outcome.

**Methods:**

This paper describes the methods of the Choose Change study that compares transdiagnostic inpatients (*n* = 85) and outpatients (n = 85) with varying degrees of treatment experience and treatment success (i.e., no previous treatment vs. previous remission vs. treatment-resistant). Patients received ACT during an intensive treatment phase lasting approximately twelve treatment sessions, and were accompanied up to twelve months following intensive treatment. Main outcomes include symptoms, functioning, and well-being. Multiple levels of data are investigated, including treatment context, weekly assessments, a behavioral approach test, multiple follow-up phases, and ambulatory assessment using Event Sampling Methodology, to examine patients’ daily context.

**Discussion:**

We aim to investigate antecedents, consequences, and inherent processes that contribute to the maintenance or fluctuations of psychological disorders and the efficacy of ACT treatment. Furthermore, this study intends to increase understanding of how accurately participants can report on their own experiences, in order to expand our knowledge of how to probe for such information in the future. The results of Choose Change will provide basic clinical theory and clinical care with important and meaningful insights into the effectiveness of ACT, trans diagnostically, in in- and outpatients, and in a naturalistic setting.

**Trial registration:**

This study was retrospectively registered in the ISRCTN Registry (registration number ISRCTN11209732) on May 20th 2016.

## Background

### Acceptance and commitment therapy

Acceptance and commitment therapy (ACT) has been shown to be efficacious in numerous disorders, such as anxiety and depression (e.g., [1]), psychosis (e.g., [2]), phobias (e.g., [3]), alcohol use, anger, and stress (e.g., [4]), obesity (e.g., [5]), burnout [6], and treatment-resistant patients [7]. ACT aims to increase psychological flexibility, which has been shown to increase mental health in over 250 randomized controlled clinical trials across numerous disorders [8]. Psychological flexibility is defined as someone’s ability to “recognize and adapt to various situational demands; shift mindsets or behavioral repertoires when these strategies compromise personal or social functioning; maintain balance among important life domains; and be aware, open, and committed to behaviors that are congruent with deeply held values” ( [9], p865). Preliminary evidence suggests that symptomatology itself does not explain whether someone is functioning with a high level of well-being [10] and there is also evidence that psychologically flexible responses to changing demands promote advantageous outcomes [11]. This speaks to a tendency in basic behavioral science and research away from disorder-specific characteristics and processes, towards processes that potentially underlie multiple disorders and clinical states [12]. However, despite ACT being a transdiagnostic approach [13], there are few transdiagnostic (i.e., applicable across diagnostic categories as opposed to a single disorder) effectiveness studies (e.g., [14, 15]). Further, despite the studies investigating ACT’s efficacy, important questions remain, for example, specification of the mechanisms of action, stability of change, and how well it can be implemented into routine clinical practice [16]. However, in clinical trials, the mechanisms of change are far from clear, and integrated assessment is as necessary as it is difficult to implement. Overall, this study investigates three key aspects: The effectiveness of ACT, long- term follow-up, and the social context and social processes.

### Effectiveness of acceptance and commitment therapy

There is also a need to improve our understanding of the effectiveness of ACT, stressing real-world settings across broad populations with the goal of maximizing external validity [17]. While the importance of Randomized Controlled Trials (RCTs) and efficacy studies is evident, such tightly controlled and randomized studies might neglect crucial factors of what is done in the field [18], and thus less likely reflect conditions under which interventions are used in common clinical practice [19]. Non-randomized trials are often more externally valid than RCTs because they include all patients, are conducted under conditions that more closely match how practitioners will ultimately implement the treatment, and include more context variables (such as patient-practitioner relationship, [20]). Objective and subjective ratings need to be assessed, for instance through paradigms assessing psychological flexibility during a psychological challenge (i.e. a behavioral approach test).

### Long-term follow-up

Relatively little is known about the processes that unfold following treatment, for instance, whether or how patients integrate newly learned skills into their daily environment, and how these factors interrelate with well-being of both the patients and their social networks. Processes following treatment have traditionally been examined with a single assessment concentrating on symptomatology, which is why researchers have been encouraged to include longer follow up periods in clinical studies [21]. The period following treatment is risky if patients stop applying what was learned during therapy or are confronted with challenges [21, 22]. This is especially true for treatment-resistant patients (i.e., patients who do not respond to standard, first line treatments), for whom viable treatment options are lacking and even less is known about than about first-line treatments [7]. To determine if ACT can meaningfully impact treatment-resistant patients in routine practice, a study population including treatment-resistant patients across diagnoses treated in real-world settings is essential. Inclusion of non-treatment-resistant patients, however, is important as well to inform about treatment-resistant ones.

### Social context and social processes

Factors outside therapy itself, including social processes, are believed to account for approximately 33% of improvement in patients undergoing psychotherapy [23]. Despite the importance of social context, it remains poorly understood how the influence of social surroundings (e.g., supportive vs. counterproductive) longitudinally affects the patient’s well-being and prosociality (i.e., cooperating with others, acting for the well-being of others, and sacrificing for others, [24, 25]) and how this in turn affects the patient’s social context. Tracking the transition into the real world after treatment is therefore crucial. The challenges and risks of relapse during this period may be more extreme for inpatients than outpatients, as their change of environment (i.e., leaving the hospital) is more extreme; however, this has not been tested directly. Furthermore, it is completely unknown how the influence of these social variables is moderated by psychological flexibility. Patients treated in an inpatient setting with more negative relationships in their extended social network have been found to relapse more frequently [26]. This suggests that both close and extended social ties are relevant for outcomes, and that these impact multiple forms of treatments. More research is sorely needed to better understand the mechanisms that influence a patient and their social context, particularly in disorders beyond depression and in non-cross-sectional studies that allow the temporal order of effects to be disentangled [27, 28]. The few existing longitudinal studies have identified a bidirectional link between couple distress and depression [27, 28] and to a lesser extent between couple distress and substance abuse [29, 30] and between couple distress and anxiety [30]. Relatively little emphasis has been placed on outcomes of functioning, well-being, or prosocial behaviors – neither in the treated patient nor the immediate and extended social network. As such, little is known about the interaction between treatment, social context, and these broader outcomes.

Building on these insights, the necessity to understand patients’ behavior in their natural environment becomes clear [31]. Daily life happens in specific environmental contexts, and there is a need to understand these contexts. Implementing Event Sampling Methodology (ESM) allows the examination of patients’ daily life and its stressors, including the assessment of moods, thoughts, symptoms or behaviors, which change over time [31, 32]. Thus, ecologically valid data can be collected in a real-time fashion while capturing dynamic changes of variables [33].

### Study aims

The major aim of *Choose Change* is to longitudinally examine the mechanisms of action involved in an ACT treatment for transdiagnostic patients with varying degrees of treatment experience and treatment success in a controlled effectiveness trial in order to maximize external validity [17]. More specifically, it will be tested how psychological flexibility training (i.e., ACT) influences various outcomes across time and document how the intervention is implemented in patients’ everyday lives following the treatment. Simultaneously, state-of-the-art methods are used to ascertain processes of change and maintain internal validity. Increased use of technological innovations, such as mobile phones, will provide us with more information about the common and specific effects of psychological treatments [34]. This is the first project to test the effects of the social context of treatment settings (in- vs. out-patient) and the transition out of intensive treatment to well-being, functionality, and recidivism following a modern transdiagnostic behavioral treatment promoting psychological flexibility.

#### Main research areas

We will investigate the immediate and long-term outcomes of treating treatment-resistant patients with psychological flexibility training (i.e., ACT) in two treatment-related social contexts (i.e., inpatient and outpatient), and the influence of other, naturally occurring social contexts (e.g., self-chosen contexts such as home, work etc.) on various treatment outcomes. These research areas include broad outcomes (i.e., indices of well-being, functioning, social interactions, and prosocial behavior) in addition to symptoms and recidivism, thus going beyond a symptom-based focus.

On the basis of these main research questions, we derived the following main hypotheses: First, we expect the ACT intervention to lead to significant and clinically relevant changes during treatment that remain stable or increase at 12-month follow-up. Second, patients treated in the inpatient setting will experience more intense and frequent social stressors in the follow-up period than those treated in the outpatient setting, which will have a negative impact on outcomes. Third, psychological flexibility will moderate the negative impact of social stress on outcomes over time, so that it is buffered in patients with high levels of psychological flexibility.

## Method

### Design

This is a controlled effectiveness clinical trial. The study contains multiple seven-day-ESM phases, four intensive follow-up assessments at 1, 4, 9, and 12 months following intensive treatment, weekly measures during treatment, and a behavioral approach test, while considering the effects of the social context of treatment settings (in- vs. outpatient), and following a modern transdiagnostic behavioral treatment promoting psychological flexibility. Figure 1 illustrates an overview of the study design.

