### Participant recruitment and selection criteria

Participants are recruited from two specialized clinics practicing ACT (inpatient and outpatient) from ongoing referral and intake procedures. Since ACT is a transdiagnostic therapy which is efficacious for many disorders, and in order to increase generalizability within this effectiveness trial, selection criteria are purposefully kept to a minimum. Inclusion criteria are: Minimum 18 years of age, ability to speak German sufficiently, present for therapy and able to attend sessions, previous treatment (i.e., ≥ 20 sessions of empirically supported psychotherapy and/or minimum dosage and length of an approved drug as recommended by international guidelines), and sign a consent statement will be included the study. In addition, for patients in the out-patient setting, patients will also be included with < 20 sessions therapy experience to enable full modelling of patients from those without treatment experience, to those with treatment experience in the outpatient setting, to those with treatment experience in the inpatient setting. Exclusion criteria include acute suicidal intent, acute substance dependency, (where the primary treatment goal is detoxification), active mania, previous experience with ACT, and inability to read or complete assessments. Otherwise all diagnoses are included (i.e. Affective Disorders, Anxiety Disorders, Somatoform Disorders, Mood Disorders, Anxiety-stress related Disorders, Somatic Disorders, Obsessive-Compulsive Disorder, Impulse Control Disorders, Gambling Disorders, and Personality Disorders). When participants enter the clinic, medication is optimized when necessary, as determined by the attending physician in consideration of patient preference. Medication is then held constant throughout the intensive treatment phase.

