In order to test whether treatment context has an impact on patients’ well-being and functioning (i.e. flourishing) [37], ACT will be administered for both in- and outpatients. For inpatients, a multidisciplinary team is involved, consisting of psychotherapists providing individual and group therapy and the nursing and support staff providing ACT specialized sessions. For outpatients, psychotherapists provide individual ACT sessions. All psychotherapists are certified for this study through attendance of several ACT trainings and provision of a certification role play video rated by a certified ACT trainer. Therapists will make choices based on ACT skills and procedures, which will all be documented following each session. This allows for the documentation of ACT’s clearly defined skills, while enabling a flexible and situationally sensitive application.

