### Analysis plan

For all analyses we will use multilevel models with time as level 1 and person as level 2 variables. These models are able to deal with the interdependence of observations across time within the same subject. Hypothesis 1 refers to a multilevel model with time as within-subjects variable and no between-subjects variable. Hypothesis 2 is based on hypothesis 1 but will contain in addition one between-subjects factor (group, 2 levels), plus the interaction between time and group, which is our primary focus. Hypothesis 3 refers to a multilevel model with social stress as predictor and psychological flexibility as mediator. Again, we will be interested in the interaction between these two characteristics, which are both time-varying within subjects.

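### H1 credits change to ACT in a study called controlled, but both settings receive ACT and H1 is tested by time alone, so it can show only change under care

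*Protocol article*

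**What the plan says.** **Label.** The Design section of the protocol article opens with "This is a controlled effectiveness clinical trial". Study aims and the Discussion use the same description.

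**Hypothesis.** Under Main research areas, H1 reads "we expect the ACT intervention to lead to significant and clinically relevant changes during treatment", with stability or further gain expected at 12 months.

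**Treatment and groups.** Under Outcome assessments, "ACT will be administered for both in- and outpatients". Under Participant recruitment and selection criteria, "Participants are recruited from two specialized clinics practicing ACT (inpatient and outpatient) from ongoing referral and intake procedures". No untreated, waiting-list or other-treatment group is described, and no randomisation to setting.

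**Model.** Under Analysis plan, "Hypothesis 1 refers to a multilevel model with time as within-subjects variable and no between-subjects variable". The two-level group factor and its interaction with time enter only for H2.

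**Medication and baseline.** The recruitment section states: "When participants enter the clinic, medication is optimized when necessary, as determined by the attending physician in consideration of patient preference". Medication is then kept constant during the intensive phase. The section on baseline assessment places consent, followed by data collection, in the first week of therapy.

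**The concern.** The label and the wording of H1 together promise a causal reading: ACT produced the change, and a control supports that. The H1 model estimates only the average course over time in people who all receive ACT. Whatever else moves scores between baseline and post or follow-up goes into the same time coefficient: natural course, regression to the mean, general care (for inpatients, a multidisciplinary team) and possibly a medication change made at entry.

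At stake is the main conclusion of the study. A significant time effect reported as the effectiveness of ACT in a controlled trial would claim more than H1 can establish. A later analysis plan cannot mend this, because it cannot supply a comparator that the design lacks.

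**Working it through.** **1. What each element can support**

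| Element | Where | What it gives H1 |
|---|---|---|
| Controlled trial | Study aims, Design, Discussion | Suggests a comparator |
| ACT in both settings | Outcome assessments | No contrast of ACT with non-ACT |
| Groups formed by clinic and referral | Recruitment section | A non-randomised contrast of settings |
| Group and time-by-group terms | Analysis plan, H2 | Not part of the H1 model |
| Time only | Analysis plan, H1 | Total change under care |
| Weekly process measure | Only between baseline and post | No pre-treatment run-in as a within-person control |

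**2. Medication.** Optimisation happens at clinic entry and baseline is collected from the first week of therapy. The article does not say which comes first. If the drug change comes shortly before or after baseline, some or all of its effect may appear between baseline and post. Keeping medication constant afterwards prevents later planned changes in that window, but does not remove a delayed effect of a change already made.

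**3. The plan's own sample size.** Inputs from Sample size: two-sided alpha 0.05, power 0.80, correlation 0.5, 75 patients within group, 150 in total between groups, about 10% dropout.

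- 150 / 0.9 = 166.7, so 167, against about 170 stated.
- 75 / 0.9 = 83.3, so 84, against 85 stated.
- SD of change = SD × √(2 × (1 − 0.5)) = SD.
- Effect implied by 75 patients: (1.960 + 0.842) / √75 = 2.802 / 8.660 = 0.32 SD (0.33 with the t distribution). This fits the small to medium effect that the section assumes without giving a number.

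These figures are consistent, and the point does not change them.

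**4. Illustration.** Suppose that ACT itself adds nothing and that all other causes produce a pre-post change of d SD. The values of d are assumptions, because the article gives none. Treating the H1 test as a paired comparison of baseline and post with correlation 0.5, the probability of significance is Φ(d√n − 1.96) + Φ(−d√n − 1.96). Completers: 170 × 0.9 = 153.

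| Assumed non-ACT change d | n = 75 | n = 153 |
|---|---|---|
| 0 | 0.05 | 0.05 |
| 0.1 | 0.14 | 0.24 |
| 0.2 | 0.41 | 0.70 |
| 0.3 | 0.74 | 0.96 |
| 0.33 | 0.82 | 0.98 |

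For d = 0.2 and n = 153: 0.2 × 12.37 = 2.47; 2.47 − 1.96 = 0.51; Φ(0.51) ≈ 0.70.

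The table does not estimate bias. It shows that rejecting the null hypothesis of no change says nothing about the source of the change.

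**The case against.** The best defence is that *controlled* can refer to the two concurrent groups. The Design section names inpatient against outpatient setting as what is being considered, and the Analysis plan makes the time-by-group interaction the main interest of H2. This stands. A reader might infer that the whole study is uncontrolled, but that would misdescribe H2. The setting contrast still offers no control for H1, since ACT is on both sides of it and it is absent from the H1 model.

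Second, the design is open about itself. The Background section on the effectiveness of ACT argues for non-randomised studies on grounds of external validity, the Analysis plan says plainly that H1 has no between-subjects variable, and H1 is phrased as an expectation. That is fair, but lack of randomisation is a different matter from lack of a comparator, and nowhere does the article limit H1 to uncontrolled change.

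Third, a reader might infer that drug changes at entry act mainly after baseline and are wrongly credited to ACT. The text does not support that as fact: the order is not stated, optimisation occurs only when necessary, and the share of patients affected is unknown. Only the possibility stands.

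Fourth, a reader might try to size regression to the mean from the planning correlation of 0.5 and a supposed elevation at entry. The article gives no such elevation, sets no score threshold on a primary outcome at entry, and uses 0.5 as a correlation between study time points, not as an untreated retest value. No figure can be drawn from it.

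Finally, recording medication changes may well be covered in the full protocol, and nothing says that they go unrecorded. So the fix does not assume that they do.

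**Conclusion.** The point holds as a mismatch between the label, the causal wording of H1 and the H1 model, all three of which the article states. H1 can establish that patients treated with ACT in these two settings change during and after care. It cannot attribute that change to ACT. Medication optimisation at entry is one named alternative cause whose timing against baseline is left open.

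The size of the non-ACT contribution is unknown. The probabilities in the illustration rest on assumed changes of 0 to 0.33 SD, the planned correlation of 0.5 and a paired-comparison approximation to the multilevel model. The conclusion does not depend on them. H2, the sample size and the choice of a naturalistic design are not called into question. The wording should be corrected, because the main effectiveness claim rests on it.

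**What to change.** - **Label.** In Study aims, Design and Discussion, describe the study as a non-randomised study of ACT in two treatment settings. State that *controlled* refers only to the setting comparison in H2 and that H1 has no non-ACT control.
- **H1.** Reword it as change in patients treated with ACT, and limit its conclusion to change during and after care.
- **Timing.** State when baseline is collected relative to medication optimisation.
- **Sensitivity analysis.** Repeat H1 with medication change at entry and its interaction with time. Where changes were not recorded, report that as a limitation. Say explicitly that this analysis does not isolate an ACT effect: drug changes follow clinical need, and the other sources of change remain.

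No comparator, extra patients or change to care is asked for. The cost is some rewording, one extra analysis and a weaker headline claim.

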**Fig. 1 Fig1:**
[figure not shown]
Illustration of the study design. *Note*. Smartphone, Heat Induction Test, Assessment is administered at Baseline, Post, and 12-month follow-up. Process assessment is assessed weekly during the intensive treatment phase by the patient, therapist, and nurse (in the case of the inpatient setting). Assessment through questionnaires and interview are administered at 1-, 4-, and 9-month follow up. BL: Baseline; P: Patient; T: Therapist; N: Nurse (only for the inpatient setting). FU-1, FU-4, FU-9, FU-12: Assessments at 1-, 4-, 9-, and 12-month follow up

